### Additional consent provisions for collection and use of participant data and biological specimens {26b}

At the Norwegian site, participants are asked if they are willing to donate a muscle biopsy and blood samples, and for those patients who accept, an additional signature is obtained on the informed consent document. The material will be stored in a project-specific research biobank at the Norwegian School of Sport Sciences.

#### Interventions

### Explanation for the choice of comparators {6b}

Usual care group: The UC group will receive protein supplementation to ensure adequate protein intake and they will receive an activity tracker. Both the intervention and control groups receive protein supplements to ensure adequate intake and activity trackers to encourage regular physical activity. This setup aims to isolate the added benefits of BFR-T. While activity trackers might boost physical activity in the control group, they also reduce drop-out rates and contamination.

### Intervention description {11a}

#### Exercise intervention

The exercise intervention will consist of home-based low load blood flow restricted resistance training 4-5 times weekly during the 1–4-week prehabilitation period and 2–3 times per week during the 5–6-week rehabilitation period. During the initial baseline visit (T0), patients who are allocated to the exercise group will receive instructions about how to perform the BFR-T exercises. Blood flow restriction is induced by pressure cuffs connected to a tourniquet system (Occlude, Aarhus, Denmark). The cuff is wrapped around the proximal part of the legs and arms to partially restrict blood flow into the muscle and occlude blood flow out of the muscle and the cuff pressure will be set at 50% of arterial occlusion pressure (AOP). The individualized cuff pressure should not cause pain. During the preoperative phase, patients will perform three sets of 20–15–15 repetitions for each exercise during the first week and for the remaining pre-operative weeks the volume will be increased to three sets of 30–15–15 repetitions. During the rehabilitation phase post-surgery, three sets of 20/30–15–15 repetitions will be performed. During BFR-T, the cuff will be kept inflated and released immediately upon completion of the third set. The weight loads used during exercise will be very low using the individual’s own body weight and resistance bands will be used for two of the exercises. Exercises consist of a warmup (5 min walking with cuffs placed on the legs), lunges, squats, push-ups, seated row with a resistance band, and biceps curls with a resistance band. The exercises and the repetitions/sets will be adjusted according to the patient's functional capacity. The home-based sessions will be monitored/supervised digitally or through telephone calls once per week. The home-based exercise setup enables participants to avoid time-consuming travel and allows participants to exercise independently, without access to a gym facility. This may be especially important to consider during and after times of a pandemic considering that this patient population may be more sensitive to infections.

### Criteria for discontinuing or modifying allocated interventions {11b}

In case of adverse events (AEs) and serious adverse events (SAEs), which are severe or unexpected AEs that pose a threat to the participant's safety, discontinuation or modification of the intervention may occur. The severity, frequency, and relationship of AEs to the study intervention are considered. If the participant's condition worsens, modifications or discontinuation of the intervention may be appropriate. Moreover, if a participant voluntarily withdraws from the study or requests discontinuation of the intervention, their decision will be respected. New scientific evidence, either from the trial or external sources, indicating safety concerns or lack of efficacy may also lead to intervention modifications or discontinuation.

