### Secondary outcomes

➢ Skeletal muscle molecular characteristics will be assessed in skeletal muscle vastus lateralis biopsy tissues from participants included in the study who agree to undergo the biopsy procedure (only at the Norwegian site: T0, T3).
◦ Myogenic stem cell count◦ Autophagy◦ Capillary number per muscle fiber◦ Macrophage infiltration◦ Markers of skeletal muscle catabolism➢ Patient-reported outcome measures (T0, T1, T2, T3, T4)◦ Self-reported fatigue assessed by means of the validated European Organization for Research and Treatment of Cancer Fatigue questionnaire (EORTC QLQ-FA12).◦ Health-related quality of life (HRQoL) assessed by means of the validated Quality of Life Core Questionnaire (EORTC-QLQ-C30)◦ Nutritional status will be assessed by means of the validated Patient-Generated Subjective Global Assessment scale (PG-SGA).➢ Physical fitness/performance/activity
◦ Physical function determined by the short physical performance battery and a submaximal and maximal (ramp) cycle test to evaluate cardiorespiratory fitness and maximal isometric muscle strength evaluated in a standardized manner (T0, T1, T2, T3)◦ Objectively measured physical activity and sedentary behavior using the Fitbit activity monitor (T0, T1, T2, T3, T4)➢ Clinical outcomes will be recorded retrospectively from the patient’s medical records (T4)
◦ Hospitalization rates◦ Blood status➢ Vital signs and anthropometrics
◦ Body composition using bioimpedance analysis (T0, T1, T2, T3)◦ Body composition using dual x-ray absorptiometry (only at the Norwegian site: T0, T3)◦ Body composition will also be measured using computed tomography (CT) scans when performed as a routine measurement for the patients (T0, T4). Thus, no extra CT scans will be conducted for the purpose of this study to minimize exposure to radiation.➢ Explorative outcomes

Patient’s experience of the exercise program, protein supplement, and activity tracker through focus group or individual interviews will take place sometime following the exercise intervention for a voluntary subset of the included participants in the exercise group.

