### Participant timeline {13}

Study outcomes will be measured at baseline (T0) and immediately (1–4 weeks) after the prehabilitation period (T1), after surgery prior to the rehabilitation period (T2), and after the 5–6-week postoperative rehabilitation period (T3). A follow-up assessment (T4) will take place 6 months following surgery. Patients with short time-to-surgery will only perform (T0) prior to surgery or will be included at (T2) for the rehabilitation period. Focus group or individual interviews will take place sometime following the exercise intervention. Hospitalization rates, prognostic- and blood markers will be assessed retrospectively at (T4) through the patients’ medical records. Baseline testing will begin immediately as participants are recruited and randomization will occur directly after the initial testing session (T0). Exercise training for the intervention group will start once participants have completed baseline testing. See Fig. 2 for an overview of the study design and measurement outcomes and time points.

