### Adverse event reporting and harms {22}

All AEs related to exercise or study measurements are recorded and reported to the sponsor. Participants in both groups are asked by the study personnel about exercise- and study measurement-related AEs in a standardized manner during all follow-up visits. In addition, the weekly telephone calls/video calls that are made to monitor exercise adherence for participants allocated to the exercise group will also be used to ask whether any potentially exercise-related AEs occurred during or since the last exercise session.

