### Frequency and plans for auditing trial conduct {23}

The trial will be audited independently by investigators from the Clinical Trials Office at Karolinska University Hospital who will perform monitoring on-site or remotely according to good clinical practice (GCP) and national regulations.

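### The SAE definition has no outcome criterion and only related adverse events are recorded, so an unrelated readmission has no stated systematic record until T4

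*Protocol article*

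**What the plan says.** Four places in the protocol article bear on this.

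- **Criteria for discontinuing or modifying allocated interventions {11b}** gives the only definition of an SAE: "serious adverse events (SAEs), which are severe or unexpected AEs that pose a threat to the participant's safety". For AEs and SAEs alike, it says that "discontinuation or modification of the intervention may occur". It then names severity, frequency and relationship to the intervention as things to weigh, and adds that a worsening condition may also justify a change.
- **Adverse event reporting and harms {22}** sets what is recorded: "All AEs related to exercise or study measurements are recorded and reported to the sponsor". Ascertainment has the same limit: whichever arm they belong to, patients will be "asked by the study personnel about exercise- and study measurement-related AEs in a standardized manner during all follow-up visits". The weekly calls, made to the exercise group only, "will also be used to ask whether any potentially exercise-related AEs occurred during or since the last exercise session". The section gives no separate rule for SAEs.
- **Secondary outcomes** and **Participant timeline {13}** place hospitalisation at the six-month follow-up: "Clinical outcomes will be recorded retrospectively from the patient’s medical records (T4") and "Hospitalization rates, prognostic- and blood markers will be assessed retrospectively at (T4").
- **Frequency and plans for auditing trial conduct {23}** says that the trial is monitored "according to good clinical practice (GCP) and national regulations".

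**The concern.** Seriousness (what happened to the patient), severity (how intense the event was) and expectedness (whether it was foreseen) are three different attributes. The definition in {11b} uses the second and third in place of the first. Severity then appears twice in that section, once inside the definition and once as a separate matter to weigh.

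This matters here because patients train at home with cuffs after major surgery, readmission is a foreseeable event, and the Discussion says that complication risk differs between the procedures now allowed. The trial runs at two sites in two countries, and the article gives no reference for what counts as expected. Assessors are unblinded except for biopsy and blood samples, and there is no independent data monitoring committee. The safety record should therefore rest on criteria that two sites would apply in the same way.

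The Objectives section also expects lower hospitalisation rates in the exercise arm. A safety record that does not take in admissions as they occur cannot speak to that expectation, or to its opposite, until T4.

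**Working it through.** The article gives no figure to reproduce. The check has three steps: read the definition as logic, pass a test case through the recording rule, and work out the interval.

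**Step 1. The definition in {11b}.** Read as written: SAE = (severe OR unexpected) AND threat to safety. For events that pose a threat:

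- severe and unexpected: SAE
- severe and expected: SAE
- not severe and unexpected: SAE
- not severe and expected: not an SAE

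If the clause about threat is attached to the unexpected events only, the last line is unchanged. Under either reading, whether the patient was admitted to hospital plays no part. A postoperative infection of moderate intensity that leads to readmission falls on the last line. If one site calls the same infection severe, it moves to the second line and becomes an SAE.

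**Step 2. The recording rule in {22}.** Take that readmission and suppose that it is judged unrelated to the training and the tests.

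- Is it recorded as an AE? No, because {22} covers related events only.
- Do the standardised visit questions ask about it? No, because they carry the same limit.
- Do the weekly calls ask about it? Only if it might be exercise-related, and only in the exercise arm.
- Would meeting the SAE definition change this? Not as written, because {22} has no SAE rule.
- Where is it captured systematically? In the record review at T4.

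So there are two separate defects. The classification problem comes from {11b}. The late systematic record comes mainly from the relatedness limit in {22}, and changing the definition alone would not cure it.

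**Step 3. The interval.** Inputs: surgery to discharge 2 to 3 weeks and rehabilitation training 5 to 6 weeks (legend of Fig. 1); T4 six months after surgery (Participant timeline {13}). Assumptions: T2 is at discharge, and six months is 26 weeks.

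- Surgery to T3: 2 + 5 = 7 weeks to 3 + 6 = 9 weeks
- T3 to T4: 26 − 9 = 17 weeks to 26 − 7 = 19 weeks

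The article says only that T2 comes after surgery and before rehabilitation. If T2 is later than discharge, the T3-to-T4 interval shortens by the same number of weeks. It is a gap between scheduled assessments, not a measured delay before anyone learns of an event.

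**The case against.** A reader might infer something stronger: that expected serious events as a class are not SAEs, that they come to light only at T4, and that they therefore never reach the decision to change or stop the intervention. The document does not support this, for three reasons.

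- The definition joins its first two terms with "or" in effect, not "and": an expected complication that is severe and threatening does qualify.
- {11b} opens with AEs as well as SAEs, and separately allows a change when a participant's condition worsens. The SAE label does not control access to that decision.
- The Discussion provides for ongoing checks of health and for adapting exercises to complications after surgery, and exercise participants are contacted weekly. Staff can be expected to hear of some readmissions during training. The T4 review collects a secondary outcome and is not presented as the safety channel.

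All three stand, and they confine the point to recording and classification.

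It can also be said that the article condenses a fuller protocol, where detailed SAE criteria may sit; that the definition appears in the discontinuation section, not the reporting section; that the article mentions GCP only for monitoring and does not set out its criteria; and that no SAE count is a listed outcome. These lower the weight of the point without removing it. The definition and the recording limit are stated text, not omissions, and a fuller safety section would have to override both. The gap in outcome criteria and the dependence on site judgement can be seen in the article itself, without recourse to GCP.

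**Conclusion.** The point holds in a limited form. As stated, the SAE definition has no outcome-based criterion, so an expected readmission judged not severe is not an SAE, and classification depends on each site's view of what is severe and what is unexpected. Because {22} records and asks about related events only, a readmission judged unrelated has no stated systematic record before T4.

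The harm is to consistent and timely safety recording. It is not a block on clinical action. The 17 to 19 weeks is only the approximate T3-to-T4 interval and rests on the two assumptions given with it. The number of events affected cannot be estimated, because the article gives no readmission rate.

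The change should be made: it is cheap, and it improves safety capture in an unblinded home-training trial. It does not threaten the primary analysis. If the full protocol already defines SAEs by outcome and records them regardless of relatedness, the remaining task is to bring the article's text into line.

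**What to change.** Change {11b} and {22} together, since neither change is enough alone.

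1. In {11b}, define an SAE by outcome, in line with the GCP commitment in {23}: death, threat to life, new or prolonged hospitalisation beyond the planned surgical stay, persistent disability, or another medically important event. Excluding the planned stay is needed, or every operated participant would have an SAE.
2. On the AE form, record severity, expectedness and relatedness as three separate fields, with one written reference for expectedness that both sites use.
3. In {22}, state that SAEs and unplanned admissions are logged whatever their judged relatedness, in both arms, at the existing T1 to T3 contacts as well as at T4.
4. Mark the source of each report. The weekly calls reach the exercise arm only, so comparisons between arms should rest on the visits and the record review, which both arms share.

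The T4 record review remains the source for the hospitalisation outcome. The cost is a revised definition, an added recording rule, a revised form and a few more forms to complete, with no new visits or staff. No stopping or treatment rule is changed.

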### Strategies to improve adherence to interventions {11c}

Patients are informed about the importance of adherence, potential benefits, and possible risks during the informed consent process. An effort has also been made to reduce the number and complexity of procedures to reduce the burden on participants, making it easier for patients to comply with the intervention. Timely feedback on participants’ progress and adherence is provided and monitoring/supervising the home-based exercise sessions through telephone calls/digitally will help track adherence to the exercise intervention and identify and address issues early, preventing them from becoming major barriers to adhere to the intervention. Patients will receive an activity tracker, Fitbit Inspire 2 (Fitbit Inc, subsidiary of Google LLC, San Francisco, CA, USA) on the wrist during all waking hours to monitor the activity levels. Protein supplement intake will be recorded through a protein intake log to track adherence.

### Relevant concomitant care permitted or prohibited during the trial {11d}

No concomitant care is prohibited during the trial.

### Provisions for post-trial care {30}

Each participant will receive an activity tracker (Fitbit Inspire 2, Fitbit Inc, subsidiary of Google LLC), and they will be allowed to retain it following the conclusion of the trial as an incentive for promoting ongoing physical activity. No harm is expected from the exercise trial since exercise has been shown to be safe and feasible in patients with cancer.

### Outcomes {12}

#### Primary outcome

The primary outcomes are skeletal muscle thickness and skeletal muscle cross-sectional area and will be determined by ultrasound at baseline (T0) and immediately (1–4 weeks) after the prehabilitation period (T1), after surgery prior to the rehabilitation period (T2) and after the 5–6-week postoperative rehabilitation period (T3). 

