### Sample size {14}

To achieve 80% power at an alpha level of 0.05 (two-tailed) from pre- to post-intervention based on a magnitude of change of 1 mm in skeletal muscle thickness [13], and a standard error of measurement of 0.8 mm [14], a total of 42 participants are required. According to previous findings [5], we anticipate that 25% of the participants may drop out of the study; therefore, a total of 52 participants will be required to confirm or refute our hypothesis.

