## Statistical methods

### Statistical methods for primary and secondary outcomes {20a}

Data will be analyzed using the IBM SPSS (Statistical Package for the Social Sciences) 26 statistical package for Windows (SPSS, Chicago, IL, USA). For the quantitative analysis, descriptive statistics, ANOVA, and chi-squared tests will be used to describe and compare baseline characteristics. For longitudinal analysis, linear mixed modeling adjusted for baseline values (T0) of the outcome will be used to detect any significant differences between the two groups from pre- to post-intervention as well as at follow-up 6 months following surgery. Group-by-time interaction will be included as a fixed effect. Corresponding effect sizes will also be calculated. Chi-squared tests and corresponding odds ratios will be calculated for hospitalization rates. All tests will be 2-tailed and statistical significance set at *p* ≤ 0.05.

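### Two primary outcomes are each tested at 0.05 with no rule on whether one or both must succeed and no named visit, so two-sided familywise error is not held at 5% (about 7% to 10% for two outcomes at one visit)

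*Protocol article*

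**What the plan says.** Under Primary outcome, the protocol article states: "The primary outcomes are skeletal muscle thickness and skeletal muscle cross-sectional area and will be determined by ultrasound at baseline (T0"). Scans follow at T1, T2 and T3. The primary aim under Objectives {7} also names both measures. No visit is singled out as primary.

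Under Statistical methods {20a}, a linear mixed model adjusted for the T0 value compares the groups from pre- to post-intervention and again at 6 months. "Group-by-time interaction will be included as a fixed effect". The level is 0.05 throughout: "All tests will be 2-tailed and statistical significance set at" that value. The section on missing data {20c} lists the data in the model as T1 to T4, so T0 enters as a covariate and not as an outcome row.

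Under Sample size {14}, the target reads: "To achieve 80% power at an alpha level of 0.05 (two-tailed) from pre- to post-intervention". The planned difference concerns one of the two outcomes only: "based on a magnitude of change of 1 mm in skeletal muscle thickness". Variability is entered as "a standard error of measurement of 0.8 mm". The conclusion drawn from these inputs is that "a total of 42 participants are required". No effect size is given for cross-sectional area.

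The article gives no testing order, no split of alpha, no adjustment, and no rule on whether one primary outcome or both must be significant.

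**The concern.** With two primary outcomes, each at the full 0.05, the trial's error rate depends on what counts as success. The article leaves that open in two ways: one outcome or both, and which visit. There are two training periods, one ending at T1 and one at T3, so post-intervention is not self-defining. The visit also affects who contributes, since some patients skip T1 and some enter only at T2. The ultrasound assessors know the allocation (Who will be blinded {17a}), which makes a late choice of outcome or visit harder to defend.

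A second ambiguity concerns the model. The group-by-time interaction is the only treatment-related term named. If someone took its p-value as the test of BFR-T, they would be testing a different hypothesis from the one that the sample size addresses.

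**Working it through.** **Inputs from the article.** Alpha 0.05 two-sided, power 80%, difference 1 mm, measurement error 0.8 mm, evaluable N 42, 1:1 allocation, two primary outcomes, three post-baseline ultrasound visits (T1, T2, T3). **Assumed, because the article gives none:** the correlation between the two outcomes' test statistics (0 to 0.9) and between visits (0 to 0.9).

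**Step 1: the plan's own figure.** n per arm = 2 × SD² × (1.960 + 0.842)² / 1².
- SD = 0.8: 2 × 0.64 × 7.849 = 10.05, so 11 per arm and 22 in total. This does not match.
- SD = 0.8 × √2 = 1.131 (a change-score SD built from the measurement error): 2 × 1.28 × 7.849 = 20.09, so 21 per arm and 42 in total. This matches.

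The 42 is therefore the size for one outcome, one comparison and the full 0.05. It contains no allowance for a second primary outcome.

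**Step 2: two outcomes at one visit, either sufficient.** If independent: 1 − 0.95² = 9.75%. With correlation, from the bivariate normal distribution:

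| Correlation between outcomes | Two-sided familywise error | Benefit direction only (nominal 2.5%) |
|---|---|---|
| 0 | 9.75% | 4.9% |
| 0.5 | 9.1% | 4.5% |
| 0.8 | 7.8% | 3.9% |
| 0.9 | 7.0% | 3.5% |

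**Step 3: both outcomes required at one visit.** Each test has level 5%, and the probability that both reject cannot exceed that of either alone, so the error is at most 5%.

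**Step 4: any of six outcome-by-visit tests sufficient.** If independent: 1 − 0.95⁶ = 26.5%. By simulation (400,000 draws per setting): 21.8% with both correlations 0.5, 15.1% with both 0.8, 11.6% with both 0.9. In the benefit direction only, the range is 5.8% to 14%.

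T4 does not add to this count, because the primary outcomes stop at T3. The interim look does not add to it either: it can stop the trial only if muscle mass is lower in the training group.

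**Step 5: what the interaction tests.** Let d1, d2 and d3 be the baseline-adjusted group differences at T1, T2 and T3. With T0 as a covariate, the null hypothesis of the interaction is d1 = d2 = d3. The treatment hypothesis at the end of the programme is d3 = 0. A constant benefit satisfies the interaction null whatever its size, so the interaction test would then reject at its 5% level only. With a benefit that grows over the visits it has some power: for 0.33, 0.67 and 1 mm, 20 per arm and SD 1.13, it rejects in about 35% of simulated trials at an assumed visit correlation of 0.5 and 72% at 0.8. Its power follows the shape of the effect over time and not the size of the effect at T3.

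**Step 6: cost of the possible remedies.**
- Fixed sequence at one visit (thickness, then area): familywise error 5%, N stays at 42.
- Bonferroni over two outcomes (0.025 each): 2 × 1.28 × (2.241 + 0.842)² = 24.3, so 25 per arm and 50 evaluable. At 21 per arm, power for thickness falls from about 82% to 73% (normal approximation).

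**The case against.** The best defence is that the visit is clear enough in context. The intervention is described as one combined pre- and postoperative programme, Recruitment {15} calls T0 to T3 the first phase, and the biopsies and DXA scans are at T0 and T3. The sample size and the analysis use the same pre- to post-intervention phrase. On that reading post-intervention means T3. Thickness and area are also two measures of one construct and probably well correlated, which puts the error at the lower end of the range. Order and adjustment are often left to an analysis plan.

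Much of this stands, and it rules out three stronger readings that a reader might infer.
- **The plan tests six comparisons and takes the best.** The article lists when scans are done; it does not say that each visit is a separate test. The 12% to 26% describes what the wording permits, not what it states.
- **The chance of wrongly claiming benefit is well above 5%.** For two outcomes at one visit, the benefit-direction error is 3.5% to 4.9%. That exceeds the nominal 2.5% but not 5%.
- **The treatment test has no power.** The article says that the interaction term is included, not that its p-value decides. Including it is also how the model yields visit-specific differences. The 5% rejection under a constant benefit follows by construction.

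What the defence does not remove is the missing success rule. The article itself declares two primary outcomes and sets 0.05 for every test. That is a stated rule that misses its level, not merely detail held back for another document.

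**Conclusion.** The point holds in limited form. If either primary outcome can support the claim at one visit, two-sided familywise error is about 7% to 10% instead of 5%. This rests on an assumed correlation between outcomes of 0.9 to 0. It is at most 5% if both must succeed at that visit, and about 12% to 26% only if T1, T2 or T3 could each count. The article does not say which of these applies, though T3 is the most natural reading of post-intervention. The interaction p-value is not a test of whether BFR-T works, and the plan should prevent its use as one; it does not currently say that it will be used so. This should be fixed before the data are analysed. It does not invalidate the design, and the sample size for thickness is unaffected.

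**What to change.** State in the protocol:
1. The primary test is the model-based between-group difference in muscle thickness at T3, two-sided at 0.05.
2. Cross-sectional area at T3 is tested at two-sided 0.05 only if thickness is significant.
3. T1 and T2 differences are secondary estimates, reported with confidence intervals.
4. The T3 contrast, not the group-by-time p-value, is the treatment test.

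This holds familywise error at 5%, keeps the full alpha for thickness and leaves the evaluable N at 42. The cost is that cross-sectional area can no longer support a primary claim alone. Because it changes the standing of a declared primary outcome while recruitment is open, it needs a protocol and registry amendment before analysis. The amendment should also say how patients who enter at T2, and so have no T0 value, are handled in a T3 contrast adjusted for T0; naming the contrast does not settle that.
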